#### **23.2.3. Reporting of additional information following immediate reporting**

When new information (e.g. course, test results, procedures, etc.) is obtained about an SAE for which an

immediate report has already been made, this information will be input into the EDC system (CRF).

#### **23.2.4. Handling of unexpected SAEs**

Unexpected SAEs are events which are judged to be adverse drug reaction (ADRs) due to the study drug, but which are not described in the package insert information for that drug; or, if they are described in the package insert, they differ in quality or severity from that description. These events are handled as follows:

##### **1) If due to cilostazol**

Otsuka Pharmaceutical co., Ltd. will report unexpected SAEs (ADRs) reported according to 23.2.2.

*Immediate reporting procedures* to the Minister of Health, Labor and Welfare or a party under contract to said Minister.

##### **2) If due to other drugs**

The director of each study center will report to the Minister of Health, Labor and Welfare or a party under contract to said Minister in accordance with Article 77-4-2 of Pharmaceutical Affairs Law and *Ethical Guidelines for Clinical Studies*.

#### **23.2.5. SAE reporting to IDMC and other collaborating clinical study institutions for the study**

The analysis officers in charge of the interim analysis in the data center will make lists and tabulate SAEs reported according to 23.2.2. *Immediate reporting procedures*, then report to IDMC members every month. Details were described in “The Independent Data Monitoring Committee Procedure Manual”. Instead of SAEs reporting to investigators at other site as prescribed by the *Ethical Guidelines for Clinical Studies*, the analysis officer will report the listed SAEs to all investigators.

These reports will not include information on treatment group in order to avoid various biases.

## **24. Evaluation of Adverse Events**

The investigator/subinvestigator will evaluate adverse events in accordance with the following:

### **24.1. Event name**

Name of disease or condition diagnosed will be used for each event if known instead of individual symptoms.

### **24.2. Event date**

Event date is the day of occurrence or confirmation of the adverse event. If diseases, symptoms, or signs existing as when consent was granted become aggravated during the observation period, the day of aggravation is considered the day of adverse event occurrence.

### **24.3. Severity**

Severity of adverse events is classified into 3 levels as follows:

1. Mild: Causing discomfort but no interference with daily activities
2. Moderate: Causing discomfort sufficient to restrict or affect daily activities

3. Severe: Cannot perform work or daily activities

#### 24.4. Seriousness

Seriousness of adverse events is classified into 2 levels as follows in accordance with 7.1.2. *Serious adverse events*.

1. Serious
2. Not serious

#### 24.5. Causal relationship with study drugs

Causal relationship with study drugs is classified according to the following 2 categories:

1. Relationship cannot be denied
4. Relationship can be denied

If an investigational drug or concomitant drug is judged responsible, the responsible drug should be identified.

[Reference for determining causal relationship with study drugs]

1. Relationship cannot be denied

Cases where any of the following reasons make a causal relationship a logical possibility:

- a If the event is suggested by package insert
- b If there is a suspected temporal relationship between study drug administration and event occurrence (e.g., development of allergic dermatitis several days after study drug administration)
- c If there is a suspected relationship between study drug discontinuation or dosage reduction and event outcome (e.g., rapid recovery of nausea following study drug discontinuation)
- d Other cases in which study drug involvement cannot be medically ruled out

4. Relationship can be denied

Cases where any of the following reasons make a causal relationship logically improbable:

- a If the event may be due to the primary disease, complications, or medical history
- b If the event may be due to age, sex, or other factors
- c If there is little chance of temporal relationship between study drug administration and event (e.g., adverse events occurring a significant period of time after completion of study drug administration)
- d If there is little chance of relationship due to observed course of event [e.g., subject recovers from event while continuing study drug administration and with no other actions taken (although possibility of habituation to study drug must be taken into account)]
- e If effects of concomitant drug are considered likely
- f If the event is considered likely to be due to chance alone (accident, spontaneous

- symptoms, etc.) (e.g., femur fracture due to being caught in a traffic accident)
- g Other cases in which study drug involvement can be medically ruled out

#### **24.6. Study drug-related actions**

The following study drug-related actions are available as responses to occurrence of adverse events:

1. Drug withdrawal
2. Discontinuation
3. Dose reduction
4. Dose increase
5. No change
99. Unknown

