#### 3.2. Inclusion criteria

Patients meeting all of the following criteria will be included:

- 1) Patients with a diagnosis of noncardioembolic ischemic stroke that developed between 8 and 180 days before the first day of observation
- 2) Patients with a responsible lesion identified by head MRI
- 3) Patients 20 to 85 years of age when providing informed consent
- 4) Patients taking aspirin or clopidogrel alone as antiplatelet therapy when providing informed consent
- 5) Patients meeting at least one of the following criteria:
  - i. At least 50% stenosis of a major intracranial artery (to the level of A2, M2, P2)
  - ii. At least 50% stenosis of an extracranial artery\*
 

\* common carotid artery, internal carotid artery, vertebral artery, brachiocephalic artery, or subclavian artery
  - iii. Two or more of the following risk factors:
    - 65 years of age or older
    - Diabetes mellitus
    - Hypertension
    - Peripheral arterial disease
    - Chronic kidney disease
    - History of symptomatic ischemic stroke (excluding the index IS for this study)
    - History of ischemic heart disease
    - Smoking (only current smokers, excluding previous smokers)
- 6) Patients able to visit the study center throughout the observation period

7) Patients who provided written informed consent for participation

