### **5.2. Criteria for changes in dosage or treatment schedule**

Dosage or treatment schedule of aspirin or clopidogrel will fundamentally not be changed during the observation period.

If a headache etc. occurs after treatment with cilostazol at a dose of 200 mg/day, the treatment will continue at a reduced dosage of 100 mg/day.

Study drug may be withdrawn in event of surgery or other invasive procedures, but the period of drug withdrawal may not last more than 4 weeks.

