### **5.3. Criteria for subject discontinuation or completion**

If it is determined that continued observation of a subject is impossible due to the following reasons, that subject will be withdrawn from the study and the reason and date for this recorded. All necessary observations and tests will be performed at this time, and efficacy and safety evaluations performed.

- 1) Subject requests discontinuation or withdraws consent
- 2) A serious adverse event occurs which makes continuation problematic
- 3) Any event described in 6.3.3. occurs

- 4) Drug withdrawal lasts longer than 4 weeks
- 5) Any other reasons which lead the investigator/subinvestigator to consider continued participation problematic

Observation will also be discontinued for patients who discontinued taking study drugs.

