## 7. DISPOSITION OF PATIENTS

The follow data summaries will be prepared for all subjects allocated to a treatment (ITT).

For the subjects for whom observations are discontinued or completed, the numbers of subjects observed for 1 year and 2 years and frequency distributions of the reasons for discontinuation/completion will be determined for each treatment group.

Discontinuation of observations: When the following criteria for discontinuation/completion are met and observations are discontinued.

Discontinuation/completion criteria

- 1) The subject requests that their study participation be discontinued or withdraws their consent

- 2) A serious adverse events occurs, making continued study participation difficult
- 3) An evaluated event occurs
- 4) The study drug is continuously withdrawn for more than 4 weeks
- 5) The investigator/subinvestigator otherwise determines that the subject's continued study participation would be difficult

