## **10. SAFETY EVALUATION**

### **10.1 Adverse events**

Events that occur between the observation start date and the observation end date (during the observation period) will be included in the analysis. Adverse event summaries according to system organ class and type of event will be prepared using MedDRA/J.

- 1) The number of patients with adverse events and their incidence (100 x no. of patients with adverse events / no. of ITT patients) will be determined according to treatment group. The incidence of adverse events will be compared between groups using the chi-square test.
- 2) Incidence will be determined according to system organ class and event type (preferred term) based on terminology conversions using MedDRA/J, and the chi-square test will be used to compare these incidences across groups.
- 3) A frequency distribution for each level of severity will be determined based on the converted terms. If the same type of event occurs more than once in the same subject, the severest of these events will be used.

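### No SAP output links adverse events to stopping, interrupting or reducing study drug, and the listed stopping criteria name only serious events

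*Supplement*

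**What the plan says.** **Collected.** Protocol v1.3 section 24 opens with "The investigator/subinvestigator will evaluate adverse events in accordance with the following". Among the items that follow is 24.6: "The following study drug-related actions are available as responses to occurrence of adverse events". Its options are withdrawal, discontinuation, dose reduction, dose increase, no change and unknown. Section 6.3.2 adds, at each visit, any drug discontinuation of 4 weeks or more with its date and reasons, and any shorter withdrawal with its length.

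**Consequence of stopping.** Protocol 5.3 lists five criteria for ending a subject's participation and adds: "Observation will also be discontinued for patients who discontinued taking study drugs". The reason and date of leaving are to be recorded.

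**Analysed.**
- SAP 7 gives the frequency of reasons for discontinuation or completion by treatment group and lists the same five criteria. The only one that mentions an adverse event is "A serious adverse events occurs, making continued study participation difficult".
- SAP 10.1 plans "The number of patients with adverse events and their incidence" by arm, then incidence by system organ class and preferred term, then severity: "A frequency distribution for each level of severity will be determined based on the converted terms".
- SAP 10.2 to 10.5 apply these summaries, wholly or in part, to drug reactions, serious events, serious drug reactions and bleeding.
- SAP 8.2.1 tabulates compliance of at least 70% or below, and whether drug was withdrawn, by timepoint and arm.

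**The concern.** The objective covers safety as well as efficacy, and for an add-on drug the number of patients who stop because of side effects is a basic tolerability result. The two arms do not start from the same position. Inclusion criterion 4 requires "Patients taking aspirin or clopidogrel alone as antiplatelet therapy when providing informed consent", so SAPT subjects carry on with a drug they already take, while DAPT subjects begin a second one. Stops caused by non-serious events are therefore more likely in the DAPT arm. If those stops are filed under reasons that do not mention an adverse event, the reason table understates side-effect stopping, and does so unevenly. No safety table corrects this, because none shows which events led to a change in study drug.

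**Working it through.** The point contests no figure in the plan, so the main check sets what is collected against what is reported. A short calculation of size follows.

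**Step 1. Collected items against planned outputs.**

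| Item collected | Where | SAP output that uses it |
|---|---|---|
| Occurrence and event term | 24.1 | 10.1 to 10.5 |
| Severity | 24.3 | 10.1, 10.2 |
| Seriousness | 24.4 | 10.3, 10.4 |
| Relation to study drug | 24.5 | 10.2, 10.4 |
| Action on study drug | 24.6 | none |
| Reasons for drug discontinuation | 6.3.2 | none (8.2.1 shows whether withdrawn, without cause) |

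**Step 2. Where a non-serious stop goes.** Take a subject who stops study drug because of a non-serious event. Under 5.3 observation ends, so the subject enters the SAP 7 table. Criterion 2 does not apply, because it requires a serious event. Criterion 3 does not apply, because no evaluated event has occurred. That leaves criterion 1 (subject request or withdrawal of consent), 4 (drug withdrawn for more than 4 weeks) or 5 (investigator judgement). None of these identifies an adverse event as the cause.

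**Step 3. Size.** From the documents: 2,000 subjects per group and 5% annual dropout (protocol 11.1), and a mean observation of 2 years (11.4.1; 2.25 years before allowing for withdrawals).

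- Dropouts per arm over 2 years: 2,000 × (1 − 0.95²) = 2,000 × 0.0975 = 195.
- Over 2.25 years: 2,000 × (1 − 0.95^2.25) = 2,000 × 0.109 = 218.

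The plan does not split these by cause or by arm.

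The rate of stops caused by non-serious events is not in the documents and is assumed here. The range runs from no difference (2% in each arm) to a doubling (2% SAPT, 4% DAPT). The half-width of the 95% CI for the risk difference is 1.96 × √(p₁q₁/n + p₂q₂/n), with n = 2,000.

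- 2% and 2%: 40 stops in each arm, none labelled as due to an adverse event. Half-width 1.96 × √(2 × 0.02 × 0.98/2,000) = 0.87 points.
- 2% and 4%: 40 and 80 stops, 40 extra on DAPT. Half-width 1.96 × √(0.02 × 0.98/2,000 + 0.04 × 0.96/2,000) = 1.96 × 0.00539 = 1.06 points. Power: 0.020/0.00539 − 1.96 = 1.75, giving about 96%.

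These figures show only that the comparison would be informative if it were tabulated. They do not measure harm from leaving it out.

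**The case against.** The best defence is that little is concealed. By arm, the SAP already shows all stops by reason, drug withdrawal at each timepoint, every adverse event (serious or not) by preferred term with a test, severity, and the same for drug reactions. An excess of side effects on DAPT and an excess of stops on DAPT would each be visible. The named safety endpoints are all analysed. That stands. It limits the point to the missing subject-level link between event and stop.

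The five items in SAP 7 are also headed as criteria, not as a closed set of reason codes, and the case report form manual is not shown, so the form may hold finer reasons. That is possible. But the SAP fixes the outputs, and nothing in it promises a finer split.

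Three stronger readings are tempting and not supported.

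- A reader might take protocol 5.2 ("If a headache etc. occurs after treatment with cilostazol at a dose of 200 mg/day") as evidence that stops for headache are expected. It links headache to continuing at a reduced dose, not to stopping. It does, however, make dose reduction relevant to the table.
- A reader might infer that 24.6 allows one code per event, so that stopping cilostazol alone cannot be recorded. The text does not say so. Section 24.5 asks for the responsible drug to be identified, and the form is unseen.
- A reader might assume much higher rates, such as 10% on DAPT. That is 200 stops from non-serious events alone, more than the 195 dropouts for any reason implied by the plan over 2 years and nearly all of the 218 over 2.25 years.

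**Conclusion.** The point holds as a minor reporting gap. The action on study drug and the reasons for drug discontinuation are collected and enter no planned output, and the one adverse-event criterion listed for the by-arm reason table is restricted to serious events. Following the SAP as listed, stopping due to adverse events is understated, probably mainly on DAPT. That direction is an inference from the design (only DAPT starts a new drug); the documents state no rate by arm. Under the assumed range, 40 stops per arm up to 40 against 80 would not be attributed to an adverse event.

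A reader might infer that the plan hides the tolerability of DAPT altogether. It does not: the stops are counted and the events are reported. Only their connection is lost. No primary or secondary efficacy result, error rate or stopping decision for the trial depends on it.

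**What to change.** 1. **SAP 10.1, new item 4.** For each arm, overall and by preferred term, give the number and percentage of ITT subjects with at least one adverse event, serious or not, that led to (a) discontinuation, (b) temporary withdrawal and (c) dose reduction of study drug. Give the between-arm risk difference with its 95% CI. The 24.6 action supplies all three rows; the 6.3.2 reasons serve as a cross-check for discontinuation.
2. **SAP 7.** Tabulate a non-serious adverse event as a reason separate from the serious one. This changes how the reason is reported, not the rule for when a subject leaves. If the form has no such category, it can be derived from 24.4 (seriousness), 24.6 (action) and the reasons recorded under 5.3 and 6.3.2.

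The cost is SAP wording and one extra table. No new visits, tests or form fields are called for, and the sample size is unaffected. The downside for the sponsor is that DAPT may look somewhat less well tolerated.

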#### **24.7. Adverse event-related actions**

Existence of therapy (a drug therapy or other treatment) and contents of the therapy conducted for developed adverse events should be recorded.

#### **24.8. Outcome**

Select one of the following 6 categories for adverse event outcomes. Record the date of death if the subject died, and the date of confirmation for relief (in process of recovery), not recovered, or unknown.

1. Recovery
2. Relief (in process of recovery)
3. Recovery with sequelae
4. Not recovered
5. Fatal outcome
99. Unknown (if follow-up investigation impossible for some reason, etc.)

### **25. Follow-Up Investigation of Adverse Events**

Follow-up investigation of adverse events will be performed according to the following procedures.

"Recovery" refers to a subject returning to original state of health following an adverse event. For adverse events consisting of aggravation of an existing disease, symptom, or sign during the observation period that was present when consent was granted, "recovery" refers to returning to the health state as of the first day of observation.

- 1) If the subject has not recovered from an adverse event as of the day of completion of observation or the day of discontinuation, the investigator/subinvestigator will explain follow-up investigations and their purpose to the subject, request cooperation, and perform the investigation within 4 weeks (the day the follow-up investigation is performed is recorded as the follow-up investigation day).
- 2) If there is no recovery of the adverse event as of the day of the follow-up investigation and a causal relationship between the study drug and event cannot be denied, the investigation should be

continued when possible until recovery or stabilization of the adverse event. If a causal relationship between the study drug and event can be denied, the follow-up investigation will conclude on the day the follow-up investigation is performed.

- 3) If a new SAE for which a causal relationship with the study drug cannot be denied is observed after the day of completion of observation (or the day of discontinuation) and before the follow-up investigation day; or if an adverse event for which a causal relationship with the study drug cannot be denied that has not been recovered from as of the day of completion of observation (or the day of discontinuation) becomes an SAE; then the investigation should be continued until recovery or stabilization of the adverse event.
- 4) If an SAE for which a causal relationship with the study drug cannot be denied is discovered after the day of completion of observation (or the day of discontinuation) or after the follow-up investigation day, it will not be investigated in the current study. Therefore, it should be reported according to Article 253 of Enforcement Regulations of the Pharmaceutical Affairs Law, but not through the EDC system.

## 26. Drug Information

Summaries of all study drugs are shown below. Refer to package inserts of each for details.

### 26.1. Aspirin

Aspirin inhibits the cyclooxygenase 1 (COX-1) enzyme, which in turn inhibits synthesis of the thromboxane A2 (TXA2) enzyme, thereby inducing platelet aggregation inhibition. COX-1 inhibitory action in platelets is irreversible because platelets cannot resynthesize the enzyme. However, COX-1 is re-synthesized in blood vessel tissue, so inhibitory effects on synthesis of prostacyclin (PGI2) are reversible and exhibit relatively rapid recovery. In addition, the metabolite salicylic acid does not inhibit COX-1 and does not display platelet aggregation inhibition.

### 26.2. Clopidogrel

The active metabolite of clopidogrel sulfate irreversibly acts on the P2Y12 subtype of platelet ADP receptors, and suppresses platelet aggregation and therefore platelet activity by inhibiting ADP binding.

### 26.3. Cilostazol

Cilostazol exhibits antithrombogenic action by specifically inhibiting phosphodiesterase 3 (PDE3), an enzyme which metabolizes cAMP, thereby inhibiting platelet aggregation. The drug also acts as a vasodilator, and has been reported to increase cerebral blood flow in ischemic stroke patients and blood flow to lower extremities in patients with chronic arterial obstruction.

## 27. Committees

The following types of committees will be established, members of which are described in 28. *Study*

*Organization below.*

### **27.1. Steering Committee**

This committee is to receive advice from the principal investigator and discuss overall operation of the study while also facilitating the study.

### **27.2. Protocol Authoring Committee**

This committee is to receive advice from the principal investigator and members of the Independent Data Monitoring Committee and perform revisions to the study protocol.

### **27.3. Independent Data Monitoring Committee**

This committee is to give advice on continuation or discontinuation of the study, as well as revision of the protocol and other issues, based on study progress, serious adverse events, event incidences, results of interim analysis, and other factors. In principal, IDMC will perform an interim review based on results of interim analysis with safety information and other data once per year. Beside monthly safety monitoring and yearly safety interim review, the committee will also perform an efficacy and safety interim review once at the mid-point of the study based on interim analysis of inter-group comparisons. Details were described in “The Independent Data Monitoring Committee Procedure Manual”.

### **27.4. Event Evaluation Committee**

This committee is to evaluate validity of subject-related data after an event (primary or secondary endpoint) occurs.

